#### Methods in analysis to handle protocol non-adherence and any statistical methods to handle missing data {20c}

We will undertake an intention-to-treat analysis to assess intervention effect.

Multiple imputation approach or a sensitivity analysis will be followed to address missing data.

#### Plans to give access to the full protocol, participant-level data, and statistical code {31c}

There are no plans for granting public access of the full protocol, participant-level dataset, or statistical code.

### Oversight and monitoring

#### Composition of the coordinating center and trial steering committee {5d}

The study will be conducted under the leadership of a Steering Committee, which will be responsible for scientific and operational guidance to the overall protocol. The Steering Committee will meet monthly in the initial phases, then quarterly throughout the project remainder. A Data Safety Monitoring Board made of experts in pediatric obesity and T2DM will provide oversight and will be assembled on an ad hoc basis.

#### Composition of the data monitoring committee, its role and reporting structure {21a}

Site initiation, ongoing monitoring, and study close out will be performed by the Quality Management in Clinical Research Group within the UofA (www.qmcr.ualberta.ca/). Interim monitoring visits will be conducted to ensure compliance with Good Clinical Practices; the study is conducted according to site specific standard operating procedures, the protocol, and regulatory guidelines.

#### Adverse event reporting and harms {22}

All adverse events will be tracked in an adverse event log and classified following the Guidance Document for Clinical Trial Sponsors: Clinical Trial Applications [81], according to their severity (serious, non-serious), expectedness (expected, unexpected), and relatedness to the study intervention (related, possible related, unrelated). All serious adverse events will be collected in the participant case report forms. All serious, treatment-related adverse events will be reported to Health Canada and the UofA Human Research Ethics Board (HREB). All serious adverse events will be followed until resolution (for those that resolve before the end of the study), or for 1 month after the end of the study unless the investigator determines that additional follow-up is necessary.

#### Frequency and plans for auditing trial conduct {23}

There are no plans for auditing trial conduct beyond the interim monitoring visits conducted by the Quality Management in Clinical Research Group.

#### Plans for communicating important protocol amendments to relevant parties (e.g., trial participants, ethical committees) {25}

All protocol amendments will be submitted to the UofA-HREB for approval before implementation, unless the amendment is necessary to eliminate an immediate hazard to the trial participants. In this case, the necessary action will be taken first, with the relevant protocol amendment following shortly thereafter. Investigators will be notified once the amendment has been approved by the UofA-HREB.

#### Dissemination plans {31a}

Findings from this trial will be disseminated at local, national, and international academic and professional conferences. It is expected that the study results will be published in scientific peer-reviewed journals.

## Discussion

This study will compare the metabolic benefits of fiber with those of metformin in adolescents with obesity, determine if metformin and fiber act synergistically to improve IR, and elucidate whether the metabolic benefits of metformin and fiber associate with changes in fecal microbiota composition and the output of health-relevant metabolites. The study will thereby assess the relationship between therapeutic intervention(s) and putative mechanisms that are hypothesized to underlie the clinical effects. Overall, we predict that the combination of MET and fiber will have a synergistic effect, being more effective than MET or fiber alone at 12 months in improving IR and BMI in the adolescents with obesity. We further predict that these metabolic benefits will be associated with changes in gut microbial composition and metabolic functions (assessed by 16S rRNA gene amplicon sequencing, fecal SCFAs and bile acids, and targeted plasma metabolomics) and measures of systemic inflammation and intestinal barrier function (assessed by plasma cytokine, LBP, and fecal calprotectin). If successful, our proposed combination therapy may help to interrupt the cycle of weight gain and IR, thereby reducing the risk for developing T2DM, a worldwide public health concern, in adolescence and adulthood.

To potentially maximize the number of responders to the dietary fiber intervention, a combination of fermentable non-viscous (oligofructose, resistant maltodextrin, acacia gum) and viscous (PGX) fibers will be used in this study, providing a complex and diverse array of substrates to the gut microbiota [29, 82]. The colonic microbiota exists as part of an ecosystem, where substantial cross-feeding occurs; metabolites produced by one bacterium are used as a substrate by another bacterium, and specific key-stone species or guilds are required to degrade a substrate [28, 29]. Therefore, a variety of substrates are likely needed to enhance and diversify microbial responses aimed at improving host metabolism. This concept is supported by in vitro evidence showing that a mixture of fibers is better than a single fiber at promoting bacterial diversity [83], which is generally lower in adolescents with obesity [7, 9]. In human trials involving fermentable fibers, a high degree of between-study heterogeneity has been reported in the clinical response to fiber [84, 85]. These inconsistencies might stem from the extensive interindividual differences in gut microbial configurations at baseline and in response to dietary fiber supplementation [48, 84, 86]. This concept is highlighted by the recent work of Hjorth and colleagues, where individuals with a higher *Prevotella*-to-*Bacteroides* ratio at baseline lost significantly more body weight and body fat on a fiber-rich diet than individuals with a lower ratio [87]. Thus, subjects with obesity and an imbalance in the composition and functionality of the gut microbiota may not possess the microbes necessary to utilize and benefit from a single-fiber supplement. Therefore, providing a mixture of fiber structures, as opposed to a single fiber, could potentially induce more reliable metabolic effects in individuals with obesity and IR.

By employing targeted fecal and plasma metabolomics with fecal microbiota sequencing, we can identify changes in metabolite production that correlate with modifications of the gut microbiota. This systematic analysis of the gut microbial community may result in the identification of baseline microbiota configurations or metabolites that predict effects of MET and/or fermentable fibers and could, therefore, be used to enhance clinical responses with personalized therapies. Such novel biomarkers might also be relevant for predicting the future risk of developing metabolic abnormalities associated with childhood obesity. Our novel approach will inform the development of future microbiome-targeted pharmaceutical and prebiotic therapies, including the possible implementation of long-term, multicenter microbiome-targeted intervention studies aimed at improving health outcomes in childhood obesity. Finally, the goal of the research team is to provide a basis for using the gut microbiome as a window to improve the assessment and treatment of metabolic abnormalities in children with obesity.

While the high dietary fiber dose and 12-month intervention period are considered strengths of study, and potentially necessary for attaining reliable and sustained health benefits linked to fiber [85], both variables may impact protocol adherence and attrition throughout the intervention. To partially mitigate this, regular clinic visits, phone calls, emails, and text messages will occur to ensure the participants’ engagement and encourage protocol adherence. We will also monitor adherence through self-documentation (dosing journal) and collecting all unused study products. Another study limitation is that features of the participant’s lifestyle (i.e., diet and physical activity) remain uncontrolled. While this “real life” approach greatly improves the generalizability of study findings, as is often the case, intentional or unintentional lifestyle changes can occur that independently improve IR and BMI. To minimize these effects, participants will be encouraged to follow the study protocol without intentional lifestyle changes. Additionally, 3-day food records and physical activity questionnaires will be completed at baseline and throughout the dietary intervention to establish deviations from baseline, which will be incorporated and controlled through statistical analysis.

In summary, this study will determine the efficacy of MET and fermentable fibers alone or in combination on metabolic control, while also determining if the effects are related to individual differences in microbiome composition and functions. Thus, this study will demonstrate whether the gut microbiome represents a promising target for enhancing therapeutic efficacy and for further preventing T2DM in at risk adolescents. The results of this study may be integrated into clinical practice guidelines for the prevention of youth-onset T2DM and also aid in the development of novel microbiota-targeted therapies for adolescents with obesity and associated metabolic comorbidities.

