**Discussion:**

This study will compare the potential metabolic benefits of fiber with those of metformin in adolescents with obesity, determine if metformin and fiber act synergistically to improve IR, and elucidate whether the metabolic benefits of metformin and fiber associate with changes in fecal microbiota composition and the output of health-related metabolites. This study will provide insight into the potential role of the gut microbiome as a target for enhancing the therapeutic efficacy of emerging treatments for T2DM prevention.

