### Trial design {8}

A single-center, parallel three-armed, double-blinded, 12-month randomized controlled trial with a 1:1:1 allocation ratio. Ninety adolescents (*n* = 30 per arm) with obesity, IR, and family history of T2DM will be enrolled in the trial matched for sex and age (Figs. 1 and 2).

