## Interventions

### Explanation for the choice of comparators {6b}

We postulate that the therapeutic effects of both MET and fermentable fibers are mediated, in part, through diverging effects on the gut microbiome, and that MET plus fiber combination therapy will act synergistically to improve glucose tolerance in adolescents with obesity and IR. By combining MET with fiber, we anticipate that the improvement in IR and BMI will be significantly higher when compared to each monotherapy. A control group without treatment is not included, since a no treatment arm would be unethical for adolescents with obesity and IR.

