### Relevant concomitant care permitted or prohibited during the trial {11d}

Hypoglycemic drugs, insulin, and medications known to affect body weight will not be allowed during the trial. If a participant must use any of these medications, he/she will be withdrawn from the study. The principal investigator will determine acceptability of any other concomitant medication. Adolescents in this study will continue to receive conventional lifestyle management advice as per routine clinical practice at their clinics.

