### Statistical methods

#### Statistical methods for primary and secondary outcomes {20a}

Descriptive statistics will summarize all study variables. Prior to analysis, numerical variables with skewed distribution will be transformed (e.g., log_2_ or cubed root) or a comparable nonparametric test will be used. Between-group comparison of primary and secondary outcomes will be performed at baseline and two consecutive time points independently using unpaired *t*-tests (comparing two groups) or analysis of variance (three groups) and chi-square tests for numerical and categorical data, respectively. Impact of the three interventions on IR (HOMA-IR, primary endpoint) over time will be compared using linear mixed models, after adjusting for relevant confounders, including pubertal stage if any statistically significant difference is observed between treatment groups at baseline. OTU relative abundance will be compared between treatment groups. Statistical analyses for gut microbiota community composition will include principal coordinates analysis and canonical correlation. Linear discriminant analysis Effect Size [78] and multivariate association with linear models will be used to identify specific OTUs that differentiate the treatment groups. Mediation modeling will be employed to provide further insights on possible casual pathways to explore whether the gut microbiota may play a causal or mediation role in the physiological effects detected [79]. Treatment responders versus non-responders will also be evaluated. We will characterize the ecological differences prior to the intervention, and then the individualized response to the intervention in order to assess the role of the microbiome in the host’s metabolic response to the intervention. For this analysis, we will apply a machine learning approach called partition around medoids clustering [80]. Separate models will be estimated for secondary endpoints, which are exploratory, but nevertheless important. Intervention types and times will be included as fixed effects in linear mixed models. Pearson or Spearman correlation coefficients will be computed between changes in gut microbiome composition/function and insulin resistance, hormones, metabolites, and inflammatory markers.

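### Three arms without a neither-agent arm can show that the combination beats each monotherapy, but not that metformin and fiber act synergistically, as the protocol says it will determine

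*Protocol article*

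**What the plan says.** Trial design {8} describes "A single-center, parallel three-armed, double-blinded, 12-month randomized controlled trial with a 1:1:1 allocation ratio". Under Intervention description {11a} the arms are metformin with fiber placebo, fiber with metformin placebo, and both active agents. Explanation for the choice of comparators {6b} says why no arm lacks both agents: "A control group without treatment is not included, since a no treatment arm would be unethical for adolescents with obesity and IR".

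The abstract's Discussion and the opening of the main Discussion both say the study will "determine if metformin and fiber act synergistically to improve IR". Later in that same opening paragraph the combination is predicted to be one that "will have a synergistic effect, being more effective than MET or fiber alone at 12 months", so synergy is equated with superiority to each single agent. Section {6b} postulates synergy and then gives the expected finding: "we anticipate that the improvement in IR and BMI will be significantly higher when compared to each monotherapy". The closing summary of the Discussion adds that "this study will determine the efficacy of MET and fermentable fibers alone or in combination on metabolic control".

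The formal parts are worded differently. Objectives {7} sets out a comparison of the three regimens on HOMA-IR and does not name synergy. Section {20a} plans between-group comparisons and states that "Intervention types and times will be included as fixed effects in linear mixed models". It names no additivity reference.

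**The concern.** In its usual statistical meaning, synergy is more than the sum of the separate effects, so it is an interaction. A 2×2 interaction needs all four cells, and this trial has three. The Discussion fills the gap by letting superiority to each monotherapy stand for synergy, but two agents that simply add their effects also satisfy that condition, as do two agents that interfere slightly with each other.

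What is at stake is the conclusion drawn from a positive trial. If the combination beats both monotherapies, the protocol's wording invites a report of synergy that the data could not separate from additivity. The word is not casual here: Background and rationale {6a} uses it for a mechanism acting through the gut microbiome, and the closing summary expects the results to inform guidelines.

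**Working it through.** The protocol gives no figure for an interaction to reproduce. Its sample size {14} concerns pairwise differences between arms and is used here only as a source of inputs.

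**1. What three arms identify.** Let M, F, C and N be the mean improvement in HOMA-IR, in SD units, with metformin, fiber, both, and neither.

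- Estimable: C − M (fiber added to metformin), C − F (metformin added to fiber), M − F.
- Interaction: I = (C − M) − (F − N) = C − M − F + N.

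N has no data. Suppose the three arm means were M = 0.75, F = 0.86, C = 1.61. Then I = 1.61 − 0.75 − 0.86 + N = N:

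| Unobserved N | Interaction I |
|---|---|
| −0.3 | −0.3 (sub-additive) |
| 0 | 0 (additive) |
| +0.3 | +0.3 (synergistic) |
| +0.6 | +0.6 (synergistic) |

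Identical trial data fit all four rows, so a larger sample does not help.

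Change from baseline cannot stand in for N. Entry requires HOMA-IR above 3.16, so some regression to the mean is expected. Participants are aged 12 to 18, and pubertal stage is a named confounder. Lifestyle care also runs in every arm: "Adolescents in this study will continue to receive conventional lifestyle management advice as per routine clinical practice at their clinics".

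**2. How often additive effects would pass the Discussion's test of synergy.**

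Inputs from {14}: effect sizes 0.75 (metformin) and 0.86 (PGX), 90 participants, 15% attrition. Evaluable per arm: 90 × 0.85 / 3 = 25.5.

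Assumptions: both effect sizes are against no treatment; the fiber mixture has the PGX effect; SD = 1; two-sided 5% per comparison; normal approximation.

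- Standard error of a difference: √(2/25.5) = 0.280.
- The two differences share the combination arm, so their correlation is (1/n)/(2/n) = 0.5.
- With interaction I, C − M = 0.86 + I and C − F = 0.75 + I.
- Power of each test = Φ(difference/0.280 − 1.96). The joint probability comes from the bivariate normal with correlation 0.5.

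| I | C − M | C − F | Power, each | Both significant |
|---|---|---|---|---|
| 0 | 0.86 | 0.75 | 87%, 76% | 70% |
| −0.2 | 0.66 | 0.55 | 65%, 50% | 40% |
| −0.3 | 0.56 | 0.45 | 52%, 36% | 26% |

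Simulated t-tests at 26 per arm agree: 69% for I = 0 and 39% for I = −0.2.

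**3. Range for the assumed effects.** If both effects were 0.5 and additive, each test has Φ(0.5/0.280 − 1.96) = 43% power and both are significant in about 27% of trials. The percentage depends on the assumed effects. Step 1 does not.

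**The case against.** The strongest reply is that the formal trial does not depend on synergy. Objectives {7} asks for a comparison of regimens, {20a} analyses between-arm differences, and the primary outcome and sample size need no interaction. The absence of an untreated arm is disclosed and given an ethical reason. The sentence on greater effectiveness at 12 months is a prediction, and it shows the reader what is meant by synergy: better than either agent alone, which these arms can test. All of this stands, and it limits the point to wording.

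It does not remove the point. The abstract and the opening of the Discussion go beyond prediction and say the question of synergy will be determined. The ethical reason explains why the arm is absent but does not supply the contrast. A looser meaning of synergy is testable, but additivity satisfies it.

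The illustration is also open to challenge. The comparators behind 0.75 and 0.86 are not shown, and PGX makes up 5 g of the 35 g fiber mixture. The percentages are therefore examples and not predictions.

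A reader might infer that improvement within a monotherapy arm will be reported as efficacy. No section plans that; the analysis is between groups. The two add-on contrasts also give randomized evidence on each agent. What is missing is each agent against neither.

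**Conclusion.** The point holds as a mismatch between a stated aim and the design. Departure from additivity cannot be estimated with these three arms at any sample size. This conclusion rests on the arm structure alone.

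The size of the risk does rest on assumptions. If 0.75 and 0.86 are effects against no treatment, both comparisons succeed in about 70% of trials under exact additivity and about 40% with an interaction of −0.2 SD, at 25.5 per arm. Smaller true effects lower these figures.

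Two stronger readings are tempting and not supported. One is that the trial is misdesigned or needs a fourth arm: the primary objective and analysis are answerable as they stand, and whether such an arm would be acceptable is an ethical matter not judged here. The other is that marked antagonism would usually pass as synergy: joint success is already down to 26% at −0.3 SD.

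Severity: should-fix.

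**What to change.** Keep the three arms, the primary objective in {7} and the between-arm analysis in {20a}.

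- In the abstract's Discussion and the opening paragraph of the main Discussion, replace the synergy aim and the synergy prediction with *whether the combination is superior to each monotherapy*.
- Align the hypothesis wording in {6b}, which already gives superiority to each monotherapy as the expected result.
- State once that no inference on synergy or additivity will be drawn.
- As a secondary edit, reword the closing summary of the Discussion to match {7}: compare the combination with each monotherapy, and the monotherapies with each other. The effect of either agent against neither is not estimable.

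The cost is a narrower claim and a few sentences. No participants, visits or assessments are added, and Trial status says recruitment had not yet started.

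For scale only: with a hypothetical fourth arm the interaction has variance 4/n. An interaction as large as 0.75 SD would need 4 × ((1.96 + 0.84)/0.75)² ≈ 56 per arm, 224 in total, for 80% power. At 26 per arm the power would be about 48%.

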Dietary fibers have been long implicated in the protection from obesity and related comorbidities [26, 27]. As dietary fibers are not digested in the small intestine, they serve as growth substrates for the gut microbiota, producing putatively beneficial metabolites such as short-chain fatty acids (SCFAs) upon degradation [28, 29]. Microbially derived SCFAs have been proposed to enhance intestinal barrier function, downregulate pro-inflammatory immune responses, alter gastrointestinal transit time, reduce hepatic-associated gluconeogenesis, improve insulin sensitivity, and promote satiety independent of GLP-1 [29–31]. Administration of SCFAs in humans has also been shown to improve glucose metabolism, systemic inflammation, and energy homeostasis [30]. In addition, consumption of diets rich in dietary fiber can limit microbial fermentation of proteins and production of potentially detrimental metabolites, such as *p*-cresol, amines, and branched chain fatty acids [29, 32, 33]. Since MET and fermentable fibers have been shown to reduce weight and increase insulin sensitivity through divergent mechanisms of action, we postulate that combination therapy with MET plus fiber will act in concert to increase insulin sensitivity in adolescents with obesity through synergistic effects on the gut microbiome.

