### Outcomes {12}

The primary outcome of this study is a change in IR, as estimated by HOMA-IR, between baseline, 6, and 12 months. The secondary outcomes of this study include changes between baseline, 6, and 12 months in (1) the Matsuda, insulinogenic, and oral disposition indices as determined by OGTT; (2) weight, BMI percentile and *z*-score, and body composition (fat mass, fat-free mass, and ratio of fat mass to fat-free mass); (3) QoL and perceived hunger and satiety; (4) fasting metabolic (glucose, adiponectin, lipids, and OGTT) and satiety markers (acylated ghrelin, PYY, GLP-1, and leptin); (5) measures of systemic inflammation (C-reactive protein, interleukin 6, and TNF-α) and gut barrier integrity (lipopolysaccharide-binding protein [LPB] and fecal calprotectin); and (6) gut microbiome composition and functions (fecal microbiome composition, fecal SCFAs and bile acids, and targeted plasma metabolomics [amino acids, branched chain ketoacids, acylcarnitines, ceramides, trimethylamine *N*-oxide, choline, and betaine]).

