### Study questionnaires

A 3-day food record (2 weekdays/1 weekend day) will be completed every 3 months to monitor dietary intake and diet quality throughout the study. Self-reported physical activity levels will be assessed every 6 months using the physical activity questionnaire for older children (≤ 14 years) [56] and for adolescents (> 14 years) [57]. QoL will be measured every 3 months using the Peds QL 4.0 instrument [58]. The validated SLIM scale will be used to assess perceived hunger and satiety (fasting, before dinner, and 1 and 2 h after dinner) every 3 months. This scale is a 100-mm visual analog scale anchored by “greatest imaginable hunger” and “greatest imaginable fullness”, with “neither hungry nor full” in the center. Participants will place a mark on the scale corresponding to their sensation of hunger or fullness [59]. To evaluate the gastrointestinal tolerance of the interventions, a previously described gastrointestinal tolerance questionnaire will be used every 3 months [33]. This questionnaire assesses the presence and severity of six symptoms over the previous 7 days, including nausea, gastrointestinal rumblings, abdominal pain, bloating, flatulence, and diarrhea. Participants will rate each symptom as “did not experience,” “no more than usual,” “somewhat more than usual,” or “much more than usual” [33]. Bowel habits will also be recorded over 4 days every 6 months by using a bowel habits diary; in this diary, participants will record bowel movement frequency and fecal consistency rated on a scale of 1 (hard) to 5 (watery) using the Bristol Stool Scale for children [60].

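### The protocol commits to controlling for diet and activity changes measured during treatment, and its open covariate list does not keep them out of the primary HOMA-IR model

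*Protocol article*

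**What the plan says.** Four parts of the protocol article bear on this.

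- **Discussion, limitations paragraph.** Lifestyle is left uncontrolled and may itself improve insulin resistance and BMI. Diet and activity instruments are therefore used at baseline and "throughout the dietary intervention to establish deviations from baseline, which will be incorporated and controlled through statistical analysis". No condition is attached, and no model, outcome or analysis tier is named.
- **Study questionnaires.** The 3-day food record "will be completed every 3 months to monitor dietary intake and diet quality throughout the study". For activity, "Self-reported physical activity levels will be assessed every 6 months". Apart from the baseline values, all of these are post-randomisation measurements.
- **Statistical methods {20a}.** The effect of the three interventions on HOMA-IR "over time will be compared using linear mixed models, after adjusting for relevant confounders, including pubertal stage". Pubertal stage is the only covariate named, and its inclusion is tied to a significant difference at baseline. The list is not closed, and it is not restricted to baseline variables.
- **Methods for non-adherence and missing data {20c}.** "We will undertake an intention-to-treat analysis to assess intervention effect".

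On mechanism, the Background says that metformin raises GLP-1, which it describes as anorexigenic, and that fiber-derived short-chain fatty acids are proposed to "improve insulin sensitivity, and promote satiety independent of GLP-1". The Outcomes section lists "QoL and perceived hunger and satiety" among the secondary outcomes, together with satiety hormones.

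**The concern.** A change in intake during treatment can be a consequence of treatment. By the protocol's account, both agents can reduce appetite, and lifestyle change can lower insulin resistance. The path from treatment to intake to HOMA-IR is therefore one the trial would expect to see. Holding intake change fixed leaves only the effect that does not pass through intake, which is a different quantity from the effect of being assigned to an arm.

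There is a second problem. Suppose an unmeasured factor such as motivation influences both intake change and HOMA-IR, and treatment also shifts intake. Participants compared at equal intake change then differ in that factor between arms, and randomisation no longer protects the comparison.

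Nor is the adjustment needed for its stated purpose. Lifestyle change that treatment does not cause is balanced between arms in expectation by randomisation.

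At stake is what the between-arm contrasts mean, including combination therapy against each monotherapy.

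**Working it through.** The plan gives no figure for this adjustment, so there is none to reproduce. The check has a reading step and an illustration.

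**Reading the sections together.** The Discussion commits to the adjustment. Section {20a}, which sets the model, neither names diet or activity nor excludes them. Mediation modelling is planned in {20a}, but for the gut microbiota, so the Discussion sentence is not a reference to it. An analyst following the document could put on-treatment diet and activity into the primary model and be consistent with the text.

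**Shrinkage.** Let *a* be the treatment effect on intake change (in SD), *b* the effect of intake change on the outcome, and *c* the remaining direct effect, with effects signed so that benefit is positive.

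- Total effect = c + ab. Effect adjusted for intake change = c = total − ab.
- The total is set at 0.75 SD, the effect size in Sample size {14}. There it describes metformin on HOMA-IR, so it serves only as a scale.
- With an assumed mediated share of 20%: 0.75 × (1 − 0.20) = 0.60 SD.
- With an assumed mediated share of 50%: 0.75 × (1 − 0.50) = 0.375 SD.

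**Simulation of the same model.** Two arms of 30 (Trial design {8}), no attrition, one post-treatment outcome, least squares, two-sided 5%, 6,000 replicates. The values of *a* and *b* are assumptions. The simulation includes the fall in residual variance that adjustment brings, which shrinking the effect alone would miss.

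| a | b | Mediated share ab/0.75 | Adjusted estimate | Power unadjusted | Power adjusted |
|---|---|---|---|---|---|
| 0 | 0.4 | 0% | 0.75 | 0.82 | 0.88 |
| 0.25 | 0.4 | 13% | 0.65 | 0.81 | 0.76 |
| 0.50 | 0.4 | 27% | 0.55 | 0.82 | 0.59 |
| 0.75 | 0.4 | 40% | 0.45 | 0.81 | 0.41 |
| 0.75 | 0.5 | 50% | 0.38 | 0.82 | 0.33 |

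The first row matters. If treatment does not move intake, adjustment does no harm and gains some precision.

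**Shared unmeasured cause.** Now let treatment have no effect on the outcome and intake change have none either, while an unmeasured factor affects intake change (coefficient *u*) and the outcome (coefficient *v*). The adjusted treatment coefficient is then biased by −a·u·v.

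| a | u | v | Bias −a·u·v | Type I error unadjusted | Type I error adjusted |
|---|---|---|---|---|---|
| 0.50 | 0.5 | 0.5 | −0.125 | 0.047 | 0.076 |
| 0.75 | 0.5 | 0.5 | −0.188 | 0.050 | 0.104 |
| 0.75 | 0.6 | 0.6 | −0.270 | 0.050 | 0.170 |

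Reversing the sign of either *u* or *v* reverses the sign of the bias, so this part can act in either direction.

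**The case against.** The strongest reply is about scope. The sentence is one clause in a limitations paragraph and names no model. The operative text is {20a}, where the one named covariate depends on a baseline difference, and where secondary endpoints are called exploratory. On that view the control of lifestyle could be meant for secondary or sensitivity work. This stands as a limit: the document does not say that the adjustment enters the primary model. It does not remove the point, because the commitment is unconditional and {20a} leaves the door open.

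A reader might infer more than the text supports:

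- *That the adjustment contradicts the intention-to-treat analysis.* Intention to treat usually fixes who is analysed and in which arm, and an adjusted model can respect that. The adjustment is in tension with the effect such an analysis is meant to give, but it is not a textual contradiction.
- *That activity is a mediator in the same way as diet.* The protocol describes appetite pathways but none from metformin or fiber to physical activity.
- *That the bias must run towards no effect.* Adjusting for a mediator shrinks an effect that acts through it, but a shared unmeasured cause can create or enlarge one. All three arms are active, so a contrast loses only the part due to the between-arm difference in intake change, which is unknown.

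The stated intent also deserves fairness. The authors aim at lifestyle change unrelated to treatment and ask participants to avoid deliberate change. Measured change in intake, however, cannot be separated into the part caused by treatment and the part that was not.

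**Conclusion.** The point holds in this form: the protocol commits to statistical control for variables measured after randomisation, one of which (intake) may by its own rationale be a mediator, and its covariate wording does not keep them out of the HOMA-IR model. If they were included, the model would not estimate the total effect of assigned treatment, and the contrast could be biased in either direction.

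The size cannot be derived from the document. It ranges from no loss, if treatment does not change intake, to an adjusted effect of 0.60 to 0.375 SD in place of 0.75 SD under assumed mediated shares of 20% to 50%. The power and type I error figures are illustrations that rest on assumed *a*, *b*, *u* and *v* and on a metformin effect size that is not the combination contrast. It would go too far to say that the planned primary analysis definitely removes part of the treatment effect, because the document never places the adjustment in that model. The wording should nevertheless be corrected, since an analysis plan that follows it could inherit the problem.

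**What to change.** Change two places together; editing the Discussion alone would leave the covariate list open.

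1. **Statistical methods {20a}.** Replace the open reference to relevant confounders with a closed list and a rule: covariates in the efficacy models are limited to variables measured before randomisation, for example baseline HOMA-IR, the age and sex strata, pubertal stage, and baseline diet and activity.
2. **Discussion, limitations paragraph.** State that changes in diet and activity during treatment will be summarised by arm and used only in analyses labelled as sensitivity, exploratory or mediation.

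The cost is a few sentences. Data collection does not change, and according to Trial status recruitment had not begun under this version. The one statistical loss is some precision if treatment does not affect lifestyle: in the illustration with a = 0 and b = 0.4, power is 0.82 without the adjustment and 0.88 with it.
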